### Interventions

2.5

Eligible participants will be randomized to take one of the following supplements orally twice daily: (1) tablet 1 (3 mg of lutein ester and 1 mg of *β*-carotene) and placebo 1 (soybean oil); (2) tablet 2 (6 mg of lutein) and placebo 1; (3) tablet 3 (6 mg of lutein and 1.2 mg of zeaxanthin) and placebo 1; (4) tablet 4 (12 mg of lutein ester and 1.2 mg of zeaxanthin) and placebo 1; (5) tablet 3 and capsule 1 (130 mg of DHA plus 325 mg of EPA); and (6) placebo 1 and placebo 2 (microcrystalline cellulose). Capsule 1 and placebo 1 are provided as a clear slightly yellowish oil encapsulated in soft gel capsules, and placebo 2 is manufactured as tablets and is matched in appearance to those containing carotenoids (tablets 1–4). The composition of supplements is presented in Table 1. All the test products and matching placebos have undergone extensive quality control testing provided by the manufacturer, under quality assurance considering stability of nutrient content and other parameters, and the presence of microorganisms, heavy metals, and pesticide residue. Furthermore, the contents of active agents are verified for each batch. Participants will be instructed to take their supplements with or immediately after a meal, and record their daily intake of trial supplements in precoded recording sheets. They will be asked to maintain their routine diet and not to take additional carotenoids and omega-3 fatty acids from supplemental sources during the entire period of 24 weeks. The lowest dose corresponded to an approximate daily intake of lutein (0.06–4.84 mg/d) and *β*-carotene (0.1–8.8 mg/d) and could be used as a reference group (40). The dosage of 12 mg lutein daily was chosen based on our previous trials (22) and the extensive intervention studies (18, 41, 42). Lutein has been determined to be “Generally Recognized as Safe” by Food and Drug Administration, and the dose selection was well below the acceptable daily intake (60 mg/d) defined by the European Food Safety Authority (43). The ratio of lutein to zeaxanthin was designed on the basis of the Age-Related Eye Disease Study 2 trial (44). Group 4 was designed to replace 12 mg/d of free lutein with 24 mg/d of lutein ester to assess the bioavailability of lutein from free or ester forms. Given that the optimal ratio of EPA to DHA was unknown (45), we selected a 2.5:1 ratio of EPA to DHA and a total dose of marine omega-3 fatty acids of 0.91 g/d, which was lower than 1 g/d used in the Memory Investigation with Nutrition for Dementia trial (EPA to DHA ratio, 3.3:1) (46), the Age-Related Eye Disease Study 2 trial (EPA to DHA ratio, 1.86:1) (44), and Vitamin D3-Omega-3-Home exercise-Healthy aging and longevity trial (EPA to DHA ratio, 1:2) (47). The chosen dosage of omega-3 fatty acids was below 3 g/day set by Food and Drug Administration, and was recognized as safe (48).

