### Statistical analysis

2.12

Analysis of the primary and secondary outcomes will be conducted following the intention-to-treat (ITT) principle, whereby participants will be included in the groups to which they were originally assigned, irrespective of compliance or loss to follow-up. Missing values on baseline covariates and follow-up data will be imputed by multiple imputation methodology (78). Investigators and participants remain blinded to treatment assignment during the trial. No interim analysis is planned.

Normally distributed values will be assessed and verified using the Shapiro–Wilk test. Descriptive summaries of quantitative variables include means and standard deviations for normally distributed variables and interquartile ranges for nonnormal variables. Categorical variables are presented as frequencies and percentages. Baseline characteristics of each arm will be compared by the two-sample t-test, one-way analysis of variance (ANCOVA) and the Wilcoxon rank-sum test for continuous variables, and chi-squared test for categorical variables.

Change in continuous outcomes at each time point will be calculated as follow-up minus baseline and be represented as the mean change and 95% confidence intervals. Change in primary and secondary outcomes from baseline at 24 weeks between study arms will be performed using ANCOVA adjusted for potential covariates. Paired t test and Wilcoxon signed-rank test will be conducted for normally and non-normally distributed data, respectively. Linear mixed effects models will be performed to evaluate differences in outcome changes over time (e.g., baseline, 12, and 24 weeks) between the intervention and control groups, with the baseline values of corresponding outcomes, stratifying variables and time-group-interactions as covariates. Multiplicative interaction terms in linear mixed effects models are used to explore interactions between genetic variations or gut microbiota and the intervention outcomes.

Sensitivity analyses will be performed to verify the robustness of the results by converting continuous outcomes into categorized values and using generalized estimating equations comparing the risk ratio between groups. Subgroup analyses will be conducted to assess the moderation of the effects of randomized intervention groups by the baseline covariates (e.g., sex, time spent outdoors, ocular exposure to ambient UV radiation, blue light exposure, screen time of digital devices, or dietary carotenoid intake).

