Statistical analyses are performed using SPSS statistical package version 22.0, and R version 3.4.0 (e.g., the lme4 package, and the lmerTest package), and a two-sided *p* ≤ 0.05 will be used to determine statistical significance.

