A thorough understanding of lutein bioavailability in relation to chemical structural complexity is necessary. Lutein can be found in the free form or esterified with fatty acids in the diet. The ester forms require prior de-esterification by intestinal enzymes and are converted into free lutein before being taken up by the enterocyte (86). Data regarding supplemental intake of free lutein or lutein esters on serum response and MPOD have shown diverging results (25–29). A study by Yoshizako et al. (28) investigated the effect of free lutein and lutein esters supplements in healthy Japanese subjects and reported significant elevations on MP and serum lutein concentration in response to 10 mg of free lutein and 20 mg of lutein esters (equivalent to 10 mg of free lutein), however no significant differences were found between the two groups. In contrast, Norkus et al. carried out a clinical trial in 72 volunteers, and noted the relative serum lutein response was significantly greater from supplements containing 12.2 mg of free lutein than from supplements containing 27 mg of lutein esters (equivalent to 13.5 mg free lutein) (26). In an RCT with bioavailability as the primary outcome, 18 subjects randomly assigned to the lutein diester formulation (equivalent to 20.7 mg free lutein) or the unesterified formulation (equivalent to 24.5 mg free lutein) showed that lutein esters were 61.6% more bioavailable than the unesterified lutein formulation with higher maximum serum concentration and ascending slope (25). The LZO trial will be performed to provide more knowledge on the bioavailability of free lutein and lutein ester.

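### Biomarkers are compared between arms as raw change with no provision for unequal variance; if all six arms share one residual variance, the free-versus-ester interval is probably too narrow

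*Protocol article*

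**What the plan says.** Protocol article, section 2.12 (Statistical analysis), fixes the scale of analysis: "Change in continuous outcomes at each time point will be calculated as follow-up minus baseline and be represented as the mean change". It then sets the 24-week comparison for every primary and secondary outcome: "Change in primary and secondary outcomes from baseline at 24 weeks between study arms will be performed using ANCOVA adjusted for potential covariates". For the repeated measurements it adds: "Linear mixed effects models will be performed to evaluate differences in outcome changes over time". The software paragraph lists SPSS and R, the latter with examples ("e.g., the lme4 package, and the lmerTest package"). The distributional safeguards are a Shapiro–Wilk check and this sentence: "Paired t test and Wilcoxon signed-rank test will be conducted for normally and non-normally distributed data, respectively".

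Section 2.8 makes serum lutein, serum zeaxanthin and erythrocyte omega-3 secondary outcomes, so these rules govern them. Section 2.5 gives arm 4 its purpose: "to assess the bioavailability of lutein from free or ester forms". Its counterpart is arm 3, which has the same zeaxanthin and the same lutein equivalent.

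**The concern.** Ordinary ANCOVA estimates one residual variance from all the arms in the model, and lme4 fits one residual variance by default. The arms differ sharply in exposure to the compounds being measured. With two units a day and the 2:1 ester equivalence under Table 1, lutein equivalent is 0 in placebo, 3 mg/d in arm 1 and 12 mg/d in arms 2 to 5.

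The Introduction and Discussion both describe wide differences between people in their response to supplementation. If people respond differently, a supplemented arm carries response variation that placebo does not. Its change scores are then expected to spread more.

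A variance averaged over all six arms would then be too small for a contrast between two high-dose arms and too large for a contrast with placebo. Free-versus-ester bioavailability is one of the trial's stated aims, and its interval and p-value would be anti-conservative.

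The written safeguards do not reach this. Shapiro–Wilk tests normality, not equality of variance. The paired and signed-rank tests work within an arm. The sensitivity analysis categorises the outcomes.

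**Working it through.** **Figure in the plan.** The document states no SD, standard error or interval width for any biomarker, so there is nothing to reproduce on this point. The sample-size arithmetic is consistent (75/0.8 = 93.75, rounded up to 94; 6 × 100 = 600) but does not bear on it.

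**Inputs from the document.**
- Six equal arms (section 2.3) and 75 per arm before dropout (section 2.4).
- Two units a day (section 2.5); 2 mg ester = 1 mg lutein (Table 1).
- Lutein equivalent: arm 1, 2 × 3/2 = 3 mg/d; arms 2, 3 and 5, 2 × 6 = 12 mg/d; arm 4, 2 × 12/2 = 12 mg/d; arm 6, 0.

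**Assumed input.** The SD of lutein change is set to 1 in arms 2 to 5, b in arm 1 and a in placebo.

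**Formula.** With equal n and one common variance, pooled variance = (4 + a² + b²)/6. For arm 4 versus arm 3 the true average variance is 1, so (reported SE)/(true SE) = r = √[(4 + a² + b²)/6], and coverage ≈ 2Φ(1.96 r) − 1. For arm 3 versus placebo, divide the pooled variance by (1 + a²)/2 before taking the root.

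| b (arm 1) | a (placebo) | pooled variance | r, arm 4 v 3 | coverage | type I error | r, arm 3 v placebo | coverage |
|---|---|---|---|---|---|---|---|
| 1 | 1 | 1.000 | 1.000 | 95.0% | 5.0% | 1.000 | 95.0% |
| 0.9 | 0.75 | 0.895 | 0.946 | 93.6% | 6.4% | 1.071 | 96.4% |
| 0.75 | 0.5 | 0.802 | 0.896 | 92.1% | 7.9% | 1.133 | 97.4% |
| 0.5 | 0.33 | 0.726 | 0.852 | 90.5% | 9.5% | 1.145 | 97.5% |
| 0 | 0 | 0.667 | 0.816 | 89.05% | 10.95% | 1.155 | 97.6% |

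The last row is the limit. Four of the six arms receive the same lutein equivalent, so the standard error cannot be more than 18.4% too small while those four share one SD.

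**Simulation** (assumed inputs, 75 per arm, no true difference between arms 4 and 3, nominal 5%).
- Six-arm ANCOVA on raw change, log-normal data: type I error 8.1–9.9%.
- Same model, additive rise with response varying between people: 6.6–10.7%.
- Same model, additive rise identical in everyone: about 5%.
- Arms 3 and 4 fitted alone: about 5%.
- HC3 standard errors in the six-arm model: 4.1–5.7% in every setting.

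**Other biomarkers, same algebra.**
- Zeaxanthin is given only in arms 3 to 5. If the other three arms have SD 0.5, pooled variance = (3 + 3 × 0.25)/6 = 0.625, r = 0.791 and coverage is 87.9% for arm 4 versus arm 3. The limit is 83.4%.
- Omega-3 is given only in arm 5. If the others have half its SD, arm 5 versus arm 3 has pooled variance (1 + 5 × 0.25)/6 = 0.375 against a true average of 0.625, so r = 0.775 and coverage is 87.1%.

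These two are illustrations. EPA and DHA are expressed as percentages of total fatty acids (section 2.9.4), and the document does not show how their spread changes with dose.

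**The case against.** The strongest reply is that the document never says all six arms enter one model with one variance. A separate ANCOVA of arm 4 against arm 3 fits the same sentence and has no such problem, and the mixed-model sentence speaks only of intervention and control groups. This stands as a limit on the claim. Still, a comparison between study arms in a six-arm trial reads most naturally as one model, and nothing restricts it to pairs. The wording allows both a valid and an anti-conservative analysis of a stated aim.

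A second reply is that residual structure is often left to an analysis plan, and that lme4 and lmerTest are named only as examples. That is fair as far as silence goes. But the article does commit to the scale and the model for these outcomes, and that model's usual error term suits them badly.

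Third, the sentence on mean change with its confidence interval need not use a pooled variance. This is correct: the exposure comes from the ANCOVA and mixed-model sentences.

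A reader might also infer that raw change is itself wrong and must give way to a log-scale ratio, since the Discussion cites earlier work in relative terms ("the relative serum lutein response was significantly greater from supplements containing 12.2 mg of free lutein"). The document does not support that. Those are findings of cited studies, while section 2.8 defines this trial's outcome as change in concentration. Nor is the log scale safe in general. In simulation, a pooled log-scale ANCOVA rejected in 0–7.3% of trials when the rise was additive. A week-24 ratio also contains the lutein present before supplementation: with an assumed 3-fold rise, an increment 61.6% larger gives (1 + 2 × 1.616)/3 = 1.41, not 1.616.

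**Conclusion.** The point holds in conditional form. It needs two conditions: the six arms share one residual variance, and change varies more in arms 2 to 5 than in placebo and arm 1. The first is the natural reading but is not stated. The second is expected from the response variability that the document describes, but no SD is given.

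Under both, type I error for lutein in arm 4 versus arm 3 is about 7–11% instead of 5%, with a ceiling near 11% if arms 2 to 5 share one SD. The ceiling weakens if they do not: with a = 0.33, b = 0.5 and the ester arm's SD 1.5 times that of the free arm, coverage falls to 86.3%. Contrasts with placebo are conservative.

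A reader might conclude that the planned intervals are certainly too narrow, or that supplemented arms are known to be far more variable. The document supports neither. If everyone responded alike, or if only the two arms were fitted, error would stay near 5%. The outcome is secondary and the effect on lutein is moderate, but the aim is a stated one and the remedy is simple.

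**What to change.** In section 2.12, for serum lutein, serum zeaxanthin and red-cell EPA and DHA, keep the change-score ANCOVA and add one of the following:

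- heteroscedasticity-consistent standard errors (HC3, for example) in the ANCOVA, with a matching robust or arm-specific variance in the mixed model; or
- arm-specific residual variances in both models; or
- for ester versus free lutein, an error term estimated from arms 3 and 4 only.

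lme4 fits a single residual variance by default, so the mixed model may need robust standard errors or another routine; the packages are named only as examples, so this conflicts with nothing. A log-scale analysis with geometric mean ratios can be added as a supplement but is not a required replacement.

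The cost is a sentence of analysis text and negligible programming, with no new data. The free-versus-ester interval widens by the factor 1/r, for example 1/0.896 = 1.12 at b = 0.75 and a = 0.5. That is the width it should have had. If the variances turn out equal, almost nothing changes.

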As the primary pigment region in the posterior pole of the retina, the macula lutea is characterized by preferential deposition of lutein and zeaxanthin [collectively termed macular pigment (MP)], and responsible for the sharpest and optimal spatial vision (11). These two xanthophyll carotenoids have been indicated to serve as blue light filters and antioxidants to protect the vulnerable photoreceptor cells against light-induced oxidative stress through protective mechanisms including the absorption of short-wavelength blue light, scavenging of free radicals and reactive oxygen species (ROS), and neutralization of photosensitizers, suggesting that they might have the capacity to prevent retinal lesions (12–15). Previous randomized clinical trials (RCTs) have demonstrated the benefits of macular xanthophylls for preventing the development and progression of age-related macular degeneration (AMD) (16–18). Existing data regarding the beneficial effect of supplementation with xanthophyll carotenoids on visual performance are largely restricted to healthy population and patients with AMD (19–21). However, their efficacy in people with long-term cumulative exposure to digital screens has not been thoroughly discussed (7, 22, 23). Given that the zeaxanthin: lutein ratio reaches a maximum in the fovea of the macula, the differential distributions of the two carotenoids imply that zeaxanthin may exert the specific effect on macular health and visual performance (24). Besides, the current knowledge on supplemental intake of free lutein and lutein esters in serum lutein concentrations and macular pigment optical density (MPOD) has shown inconsistent results (25–29). As the major structural lipid avidly retained in retinal photoreceptor outer segments (POS) (30, 31), omega-3 fatty acids [docosahexaenoic acid (DHA, C22:6n-3) and eicosapentaenoic acid (EPA, C20:5n-3)] have been postulated to confer protective roles in the normal growth and development of neurons and RPEs through pleiotropic mechanisms such as suppressing oxidative stress, modulating inflammation, and inhibiting angiogenesis (32, 33), all of which have been implicated in the etiology of AMD (34, 35). Nevertheless, it remains unknown whether supplemental intake of lutein, zeaxanthin and omega-3 fatty acids has synergistic effects on macular morphology and visual function (36, 37). Thus, such an RCT related to the additional consumption of omega-3 fatty acid supplements should be conducted to provide valuable insights on these associations. Furthermore, emerging evidence has shown that the wide-ranging interindividual variability in response to nutrient supplementation is particularly affected by multiple factors, including race, genetic variations, and gut health (38, 39); to date, the majority of previous randomized trials using similar interventions were conducted in Caucasian. The role of the genetic variation at specific genes and composition of the gut microbiome in modulating the effects of lutein, zeaxanthin, and omega-3 fatty acid supplements on the vision system are yet to be explored, especially in Asian populations.

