### Primary and secondary outcomes

2.8

The primary outcome is the change in MPOD over the course of the trial. Secondary outcomes include the change in the comprehensive test battery for visual function [best-corrected visual acuity (BCVA), CS, GS, critical flicker fusion (CFF), reaction time, visuognosis persistence, in-depth assessment of dry eye disease (DED) diagnosis and symptomatology, retinal thickness, and optical quality], changes in the concentrations of serum lutein and zeaxanthin, and erythrocyte membrane omega-3 fatty acids at each time point, the compositional changes in the intestinal microbiota before and after supplemental intake of lutein, zeaxanthin, and omega-3 fatty acids, and determination of whether changes in primary and secondary outcomes are associated with genetic variations, baseline microbiome characteristics, and changes in intestinal microbiota.

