#### DNA extraction and genome-wide genotyping

2.9.5

High quality DNA samples will be purified from the buffy coat using the Genomic DNA Extraction kits according to the manufacturer’s instructions. Genome-wide genotyping will be carried out using the Affymetrix Axiom^®^ Array Automated Workflow, following the manufacturer’s protocol (64, 65). DNA stock solutions are amplified and fragmented into base pair fragments. These fragments are purified, resuspended, and then hybridized to Affymetrix Axiom^®^ Arrays. Hybridization, ligation, washing, staining, and scanning are automatically processed on the GeneTitan Instrument (Affymetrix). Finally, the genotypes of total genomic DNA for each sample are obtained through the Genotyping Console program (Affymetrix). Data management is performed on a High Performance Computing cluster. Quality control filters are applied to study samples and genotyping (e.g., genetic sex matching self-reported sex, per-sample missing rate < 10%), single nucleotide polymorphisms (SNPs) with minor-allele frequency > 1%, SNPs with a genotyping success rate of ≥95%, and Hardy–Weinberg Equilibrium *p*-value >1 × 10^−6^.

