Evidence regarding the wide-ranging interindividual variability in response to nutrient supplementation has been well described in previous studies (93–95). Similarly, the intestinal uptake or efflux, absorption, metabolism, and tissue response of dietary carotenoids and omega-3 fatty acids are particularly influenced by ethnic origin, genetic variations, and gut microbiota (38, 39). Genetic variants in genes encoding for numerous proteins involved in carotenoid metabolism could modulate the bioavailability of dietary carotenoids by affecting the expression or activity of these proteins (96, 97), which would explain the interindividual variability of the differential visual improvement achieved by individuals assigned to the same intervention. Moreover, a recent systematic review of animal studies suggests the association between carotenoids and intestinal bacteria related to both inflammation and short-chain fatty acid production (98), prompting that the interrelationship between gut health and dietary carotenoids may play a pivotal role in the initial of retinopathies. Therefore, an additional goal of this trial is to assess the impact of supplementation with xanthophyll carotenoids and omega-3 fatty acids on host intestinal health, and explore whether genetic variations, gut microbiota composition, and changes in intestinal microbiota interact with the dietary effects on MPOD and visual performance, seeking underlying mechanistic insights into interindividual differences.

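### The single p ≤ 0.05 rule also covers the gene and microbiome interaction analyses, and post-randomisation microbiota change is treated as an effect modifier

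*Protocol article*

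**What the plan says.** All references are to the protocol article.

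- **Model (section 2.12).** "Multiplicative interaction terms in linear mixed effects models are used to explore interactions between genetic variations or gut microbiota and the intervention outcomes".
- **Threshold (end of section 2.12).** "a two-sided *p* ≤ 0.05 will be used to determine statistical significance". No other threshold appears, and no analysis is exempted.
- **Status (section 2.8).** The secondary outcomes include compositional change in the microbiota, and also whether changes in the primary and secondary outcomes are "associated with genetic variations, baseline microbiome characteristics, and changes in intestinal microbiota".
- **Genotyping (section 2.9.5).** "Genome-wide genotyping will be carried out using the Affymetrix Axiom^®^ Array Automated Workflow". The quality filters keep "single nucleotide polymorphisms (SNPs) with minor-allele frequency > 1" per cent. No other frequency limit is stated.
- **Scope of the genetic question (Introduction).** The gap to be filled is described as "The role of the genetic variation at specific genes and composition of the gut microbiome in modulating the effects" of the supplements.
- **Microbiota change (Discussion).** The additional goal is to assess the effect of supplementation on intestinal health and also to explore whether "changes in intestinal microbiota interact with the dietary effects on MPOD and visual performance".
- **Sampling times (section 2.7 and Table 2).** Stool is collected at baseline and week 24 only.

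**The concern.** Effect modification by genes and gut microbiota is what the trial's precision-nutrition aim rests on, and it has secondary-outcome status. Three features make such claims unreliable if the text is followed as written.

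1. A per-test 5% rule is applied to a family of tests that must contain several SNPs, several taxa, a long visual-function battery and up to five active-versus-placebo contrasts.
2. The only frequency limit admits SNPs so uncommon that an arm of 100 may contain no carrier.
3. Microbiota change is treated both as a result of the supplement and as a modifier of its effect. It is known only at week 24, the primary time point for MPOD, so it cannot be shown to precede the response that it is meant to modify. Participants who share a given microbiota change in two arms are not groups formed by randomisation.

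The primary MPOD comparison is not affected.

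**Working it through.** **The plan's own figures (section 2.4).** 75 evaluable per arm with 20% dropout: 75/(1 − 0.20) = 93.75, so 94, as stated. Enrolment is then set at 100 per arm, which is the n used below unless noted. No standard deviation is given, so 75 itself cannot be reproduced. Solving 75 = 2(1.960 + 0.842)²/d² gives an implied standardised difference of d = 0.457, used below as a yardstick.

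**Multiplicity.** The number of tests m is an assumption. Expected false positives = 0.05 × m. Family-wise error = 1 − 0.95^m for independent tests.

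| m (assumed) | Expected false positives per outcome and contrast | Over five active-vs-placebo contrasts | Family-wise error (one outcome and contrast) |
|---|---|---|---|
| 20 | 1 | 5 | 64% |
| 50 | 2.5 | 12.5 | 92% |
| 300,000 | 15,000 | 75,000 | about 100% |
| 700,000 | 35,000 | 175,000 | about 100% |

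Correlation between nearby SNPs leaves the expected counts unchanged but reduces the number of distinct false signals.

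**Share of significant results that are false, candidate list.** Assume 5 true interactions among 50 SNPs, each of 0.457 SD, at 20% allele frequency. The carrier proportion is c = 1 − 0.80² = 0.36. The interaction SE, in SD units, is √[2/(nc) + 2/(n(1 − c))] = √(2/36 + 2/64) = 0.295. Power at 0.05 is Φ(0.457/0.295 − 1.96), about 34%. The false share is (0.05 × 45)/(0.05 × 45 + 0.342 × 5) = 2.25/3.96 = 57%.

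**Sparse carriers.** Expected carriers per arm = n[1 − (1 − q)²]. P(no carrier in a given arm) = (1 − q)^(2n).

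- q = 1%: 100 × 0.0199 = 1.99 carriers. P(none) = 0.99^200 = 13% (0.99^160 = 20% with 80 completers). P(at least one of six arms has none) = 1 − (1 − 0.134)^6 = 58%.
- q = 5%: 100 × 0.0975 = 9.75 carriers. P(at least one of six arms has none) is about 0.02%.
- Power at p ≤ 0.05 for a 0.457 SD interaction is 6.6% at q = 1% and 16% at q = 5%.

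**Microbiota change as moderator.** Two arms of 100 were simulated 4,000 times with an arm effect of 0.457 SD and a true interaction of zero. An unmeasured shared cause acts on the outcome with weight 0.5 and also on the moderator.

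| Moderator | Rejection of the interaction at 5% | Mean estimated interaction |
|---|---|---|
| Baseline value | 5.3% | 0.00 |
| Change; shared cause acts equally in both arms | 5.2% | 0.00 |
| Change; weight of the shared cause 0.2 on placebo, 0.8 on active | 13.8% | 0.15 |

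The third row can be checked by hand. The within-arm slope is covariance/variance: 0.5 × 0.2/(0.04 + 0.36) = 0.25 on placebo and 0.5 × 0.8/(0.64 + 0.36) = 0.40 on active. The difference is 0.15 with no true interaction. In the second row the interaction is unbiased, but the arm effect adjusted for change (no interaction term) falls from 0.457 to 0.33.

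**The case against.** The strongest reply is that this is a condensed article. SNP sets, genomic thresholds and FDR rules normally sit in a SAP, and the closing line of section 2.12 is a generic statement. The verb in section 2.12 is to explore. The Introduction speaks of specific genes, and the Discussion of genes for proteins of carotenoid metabolism. The 1% figure is listed with call rate and Hardy–Weinberg equilibrium as a genotyping quality filter. On microbiota, section 2.12 does not say whether baseline level or change is meant, its subgroup analyses use baseline covariates only, and section 2.8 asks about association. Only the Discussion makes change interact with the dietary effects.

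Much of this stands, and it rules out three stronger readings:

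- **That every SNP on the array will be tested by arm at 0.05, so that false signals will dominate.** The article fixes genome-wide genotyping, not a genome-wide interaction scan, and gives no SNP count. The figures of 15,000 to 35,000 are conditional on both.
- **That the 1% filter makes the genetic analysis unworkable.** It bites only for SNPs near its edge, and it does not define the analysis set.
- **That a microbiota-change interaction is necessarily biased.** In the simulation it was biased only when the arm altered how the shared cause drives the change.

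The point itself survives, because it concerns what the article states and not what it omits. The 5% rule is given without exception, and the questions are listed as secondary. Even the short candidate list that the Introduction suggests produces false positives at a rate that the rule does not control. The word explore does not remove the secondary status.

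**Conclusion.** The concern holds in this form: the stated p ≤ 0.05 rule is too weak for the gene and microbiome interaction analyses, and microbiota change should not serve as an effect modifier. It should be corrected.

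On the mildest assumption tried (20 to 50 independent candidate SNPs), 1 to 2.5 false positives are expected for each outcome and contrast. The 57% false share further assumes that one candidate in ten is truly interactive at 0.457 SD. SNPs near 1% frequency rest on about two carriers per arm and have under 7% power for an interaction as large as the implied main effect. For microbiota change, the rejection rate of 13.8% instead of 5% shows a possible bias under one assumed mechanism and does not predict this trial's error. Whatever its size, the comparison is not protected by randomisation, and the same variable is an outcome in section 2.8.

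**What to change.** 1. In section 2.12 or the SAP, replace p ≤ 0.05 for these analyses with FDR control (for example 5%) over a pre-listed set of carotenoid and fatty-acid gene SNPs, and likewise over taxa. State which outcomes and arm contrasts form the family.
2. Label any wider scan of the array hypothesis-generating. Genome-wide Bonferroni control is possible but nearly powerless here: at 5 × 10⁻⁸ with 100 per arm, power for a 0.457 SD interaction is below 0.01% at allele frequencies of 1 to 30%.
3. Set a minimum carrier count or allele frequency for arm-interaction tests. A 5% frequency, about 10 carriers per arm, is one reasonable choice among several, and power there is still low (16% in the calculation above).
4. Use only baseline microbiota as a moderator. Analyse microbiota change as an outcome by arm, or in a labelled mediation analysis with its assumptions stated, and align the Discussion with this.

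The change is to analysis wording only, with no new participants, visits or samples. The price is fewer nominally significant exploratory results, and less common variants drop out of the arm-interaction tests.
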